### Data analysis

The latest version of The Statistical Package for Social Science (IBM SPSS Statistics) version 19is used for data analyses. Intention-to-treat analyses (ITT) used to account for deviations from random allocation and missing data. A repeated measures design will be used with primary and secondary measures as dependent variables, group as the between-subjects factor, and time of measurement as the within-subjects factor.

Possible confounding variables (for example, duration of complaints) will be considered and included as covariates according to the results of correlation analyses. Effect sizes (Cohen´s d) will be calculated to determine the magnitude of the mean differences between groups on the outcome variables. According to Cohen´s guidelines, an effect size of .2 indicates a small effect, .5 a medium effect and .8 a large effect [52]. We consider a 30% reduction on the NRS to indicate clinically important change on the core outcome measure of pain intensity [53]. The economic evaluation consisted of a cost-utility analysis and a cost-effectiveness analysis. For both analyses, the incremental cost-effectiveness ratio (ICER) was calculated as (C1-C0)/(E1-E0) where C is the cost and E is the effect and the experimental and comparator conditions are indexed with the 1, 0 subscripts.

The incremental cost-utility ratio will focus on the net costs per quality adjusted life years (QALY) gained. The cost-effectiveness ratio focuses on the net costs per reliable and clinically improved case of disability/pain. Probit analysis will be used for dose–response effects. This approach based on probability theory and includes determining the observed rates and resulting probability of a response for a particular treatment.

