### Patient allocation and randomization

Patients are randomized to one of three conditions following a predetermined and computer-generated randomization schedule, pre-stratified by degree of pain catastrophizing (PCS) [28] and disability (PDI) [29]. The median scores of the pain catastrophizing and disability data from a previous study are used as cutoffs. Within each stratum, a randomized block design with a block size of nine is used to ensure equal distribution of important patient characteristics. The randomization procedure is performed by a blinded research assistant who prepares sequentially numbered, sealed, opaque envelops. As is common in psychological treatments, it was not feasible to blind patients or therapists to treatment condition.

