### Data collection

Data are collected at baseline (T0), after 10 sessions (T1, completion of EXP short), upon completion of the intervention (T2), and six months following completion of treatment (T3). Thus, participants in the short version of EXP complete only three assessments. Questionnaires are completed at home via the internet. This procedure reduces missing data and helps to keep study therapists blind to outcome data. Supplemental evaluations are carried out weekly, including process variables. If patients do not have internet access the assessment are provided on a computer in our outpatient clinic. Video recordings are carried out during each session to gather objective data for later analysis of treatment fidelity.

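### The plan lets unspecified correlation analyses choose the covariates, instead of fixing the outcome's baseline value and the randomisation strata as covariates, which costs precision and leaves the model open

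*Protocol article*

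**What the plan says.** Under Data analysis, the primary and secondary measures are dependent variables in a repeated-measures design with "group as the between-subjects factor, and time of measurement as the within-subjects factor". Under Data collection, baseline (T0) is one of the measurement times, followed by T1 (after 10 sessions), T2 (end of treatment) and T3 (six months later). Patients in the short exposure arm have one assessment fewer: "participants in the short version of EXP complete only three assessments".

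The covariate rule is a single sentence: possible confounders, with duration of complaints as the example, are to be "included as covariates according to the results of correlation analyses". It gives one example, no closed list and no threshold, and it does not say what is to be correlated with what.

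Under Patient allocation and randomization, allocation is stratified by catastrophizing (PCS) and disability (PDI), each split in two: "The median scores of the pain catastrophizing and disability data from a previous study are used as cutoffs". That makes four strata. PDI is also one of the primary outcome measures. The Data analysis section does not name either stratifier as a model term.

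**The concern.** Three features act together.

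- **Baseline.** It is used as a repeated measure and not as a covariate. The group by time test then compares changes from baseline, which is less efficient than comparing follow-up values given baseline.
- **Strata.** The design balances the arms on PCS and PDI. If these predict outcome and are left out of the model, the standard errors are wider than the design warrants. Under the stated rule, their inclusion depends on what the trial's correlations show.
- **Covariate choice.** Randomisation makes baseline imbalance a matter of chance, so a correlation screen does not identify confounding. With four primary measures (PDI, QBPDS, diary pain rating, DSF pain scale) and a longer list of secondary ones, the rule can give each outcome a different model, and nothing stops the choice being made after results are seen.

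At stake are the precision of the comparisons in research questions 1 (exposure against CBT-P) and 2 (long against short exposure), and the reader's confidence that the model was not picked.

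**Working it through.** **Inputs.** From Sample size calculation: effect 0.2 for group by time, three groups, alpha 0.05, stated β of 0.95, correlation 0.5, 36 per group, 108 in total. Assumptions: 0.2 is Cohen's f; 0.95 is power; two measurements, since the number is not stated; equal SD at baseline and follow-up.

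**The plan's own figure.** For the within-between F test, λ = f²·N·m/(1−ρ), with (k−1)(m−1) and (N−k)(m−1) degrees of freedom. With m = 2 and N = 108, λ = 0.04 × 108 × 2/0.5 = 17.28 on 2 and 105 df, giving power 0.965. The smallest N for 0.95 is 100, or 102 with equal groups, so 108 is not reproduced exactly. Rounding 102 up to whole blocks of nine gives 108, but the article does not give that reason. With m = 3 or 4 the equal-group N is 81 or 69. The mismatch does not affect this point.

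**Change score against baseline as covariate** (baseline and one follow-up, in units of SD²):

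- Change: 2(1−ρ) = 2 × 0.5 = 1.00
- Baseline as covariate: 1−ρ² = 1−0.25 = 0.75
- Ratio: (1−ρ²)/[2(1−ρ)] = (1+ρ)/2, which never exceeds 1

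| ρ | Ratio | Variance saved |
|---|---|---|
| 0.3 | 0.65 | 35% |
| 0.5 | 0.75 | 25% |
| 0.6 | 0.80 | 20% |
| 0.7 | 0.85 | 15% |
| 0.8 | 0.90 | 10% |

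At ρ = 0.5, 36 patients per arm give the precision of 36/0.75 = 48.

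**Standard errors for the research questions at ρ = 0.5, in SD units:**

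- Long v short (36 v 36): √(1.00 × 2/36) = 0.236, against √(0.75 × 2/36) = 0.204
- Both exposure arms pooled v CBT-P (72 v 36): √(1.00 × (1/72 + 1/36)) = 0.204, against √(0.75 × (1/72 + 1/36)) = 0.177

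**Three-group test with baseline as covariate.** λ = 17.28/0.75 = 23.04 on 2 and 104 df gives power 0.992 at N = 108. The smallest N for 0.95 falls from 100 to 76.

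**Strata.** The article gives no correlation between strata and outcomes, so the gain from adding them cannot be computed.

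**Type I error of the covariate rule.** Simulation of 6,000 null trials per setting: 3 × 36 patients, analysis of change, 5 or 10 independent normal candidate covariates, of which either none or three were related to change. The Monte Carlo standard error near 0.05 is √(0.05 × 0.95/6000) = 0.003.

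| Candidates | Related to change | No covariate | Entered if correlated with change at p < 0.05 | Most favourable of none or any one |
|---|---|---|---|---|
| 5 | none | 0.051 | 0.051 | 0.064 |
| 5 | three | 0.051 | 0.051 | 0.078 |
| 10 | none | 0.048 | 0.047 | 0.070 |
| 10 | three | 0.054 | 0.057 | 0.096 |

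The screen applied as a fixed rule stays near 0.05. The last column needs a choice made after the results are known.

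**The case against.** **Both models are valid under randomisation, so this is a preference.** Both are valid, but baseline adjustment has the smaller variance at every correlation below 1, for the price of one degree of freedom. The objection does not remove the point.

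**The article condenses a fuller protocol, and the strata may be in the analysis plan.** This stands in part. Silence about strata alone would be weak evidence, and the text does not exclude them. But the article does state a rule for choosing covariates, and that rule leaves the strata to the correlations. For the PDI outcome, the stratifier's own baseline already enters as T0.

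**The change-score equivalence is a two-wave result.** This stands. It is exact for baseline against one follow-up. The planned analysis has four waves in two arms and three in the short arm, so the 25% applies to each single-follow-up contrast and not to the full interaction.

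**Stronger readings that the document does not support.**

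- A reader might infer that baseline is missing from the model. It is there, as the first level of time; it is only not a covariate.
- A reader might infer that covariates are chosen by their correlation with outcome. The text does not say whether the correlations are with outcome, with group or among baseline variables.
- A reader might infer that correlation screening itself inflates alpha. The simulation shows almost no effect unless the model is picked after the event, and the article does not propose that.
- A reader might infer that the trial is underpowered. On its own assumptions for the three-group test it is not.

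**Conclusion.** The point holds as a worthwhile improvement in method, not as an error that invalidates the trial. The covariate rule is open and depends on the data, the strata are not fixed as model terms, and baseline is used in the less efficient way. At the protocol's correlation of 0.5, a contrast of baseline with one follow-up carries 1.00 SD² of residual variance where 0.75 SD² is available; the saving is 35% to 10% if the correlation is 0.3 to 0.8. This assumes equal SDs at both times. The loss falls on the comparisons in research questions 1 and 2. The three-group test has power of about 0.965 as planned and 0.992 with adjustment, reading 0.2 as f with two measurements. The gain from the strata is unknown. The type I error risk, about 0.06 to 0.10, is conditional: it needs someone to use the freedom that the open list and absent threshold leave.

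**What to change.** Replace the correlation-based sentence with a covariate set fixed for every primary and secondary outcome: the baseline value of that outcome plus the PCS and PDI randomisation strata. When PDI is the outcome, continuous baseline PDI replaces its high/low indicator. An outcome with no pre-treatment value, such as global perceived effect, is adjusted for the strata only. Compare arms at post-treatment and at six-month follow-up given baseline. Confine any other baseline covariate, such as duration of complaints, to a sensitivity analysis listed before outcome analysis starts; a dated list is better than a reference to unblinding, since patients and therapists are not blinded.

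The cost is analysis wording only. The strata are known from randomisation and T0 assessments are already planned. The sample size was based on group by time, but 108 remains sufficient on the same assumptions. With 71 of 108 patients randomised by May 2013, the set could still be fixed before the final data are available.

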### Intervention

We translated and adapted the protocol of [name] and [name] [7] for implementing EXP in a German outpatient setting. The intervention is delivered by two PhD students who are clinical psychologists and who received two different sessions of training from [name] and [name]. In addition, each session is supervised afterwards by experienced psychologists. The control condition is a cognitive behavioral treatment for pain patients containing basic elements for the management of chronic pain that are standard in our outpatient clinic. The treatment includes graded activity, relaxation (progressive muscle relaxation) and cognitive interventions such as cognitive restructuring (Table 1). Both interventions are offered in a structured, individual setting with weekly appointments of 50 minutes.

**Table 1 T1:** Overview treatment sessions

**Session**	**EXP_long**	**EXP_short**	**CBT_P**
1	Anamnesis	Anamnesis	Anamnesis
2	Psycho-educational part I	Psycho-educational part I	Psycho-educational part I
3	Psycho-educational part II:	Psycho-educational part II:	Goal setting
	Fear-avoidance model	Fear-avoidance model	
4	Fear hierarchy	Fear hierarchy	Behavior analysis
5	Exposure 1	Exposure 1	Graded Activity I
6	Exposure 2	Exposure 2	Graded Activity II
7	Exposure 3	Exposure 3	Health Behavior
8	Exposure 4	Exposure 4	Progressive Relaxation I
9	Exposure 5	Exposure 5	Progressive Relaxation II
10	Exposure 6	Completion	*Cognitive Intervention I:* Attention Shifting
11	Exposure 7		*Cognitive Intervention II:* Identification of automatic thoughts and core beliefs about pain
12	Exposure 8		*Cognitive Intervention III:* Restructuring of dysfunctional thoughts and beliefs
13	Exposure 9		Individual Session I
14	Exposure 10		Individual Session II
15	Completion		Completion

CBT-P, Cognitive behavioral treatment for chronic pain problems*;* EXP*,* Exposure treatment.

Treatment sessions are video-recorded and a random selection of videos is evaluated for treatment fidelity. Two blinded raters independently assess protocol adherence, treatment contamination and whether the treatments can be differentiated from each other using the method of assessing treatment delivery in clinical trials (MATD) [30]. In advance, treatment elements of both treatments were identified and listed in a randomized order for the ratings.

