#### Secondary outcomes

Fear of movement/pain anxiety is measured using the Tampa Scale of Kinesiophobia (TSK) [23,35] and The Pain Anxiety Symptom Scale (PASS) [36,37]

Pain catastrophizing is assessed using the Pain Catastrophizing Scale (PCS) [28,38].

Emotional distress is measured using the Hospital Anxiety and Depression Scale (HADS) [39,40].

Quality of Life is measured using the EuroQol Questionnaire (EQ-5D) [41,42].

Pain vigilance is measured using the Pain Vigilance and Attention Questionnaire (PVAQ) [43,44].

Physical activity is assessed using the International Physical Activity Questionnaire (IPAQ) [45].

Global perceived effect of treatment is rated on a 7-point scale (1 = completely recovered, 7 = worse than ever) to assess subjective perceptions of recovery.

All instruments have been widely used and demonstrated reliability and validity in the chronic pain population.

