### Economic evaluation

Costs and expenses are evaluated using an adapted version of the short form of the Trimbos/iMTA questionnaire for costs associated with psychiatric illness over the past month (TIC-P) [51]. The total costs include direct health-care and non-health care costs (that is, travel costs, out-of pocket expenses, self-paid medical care), as well as indirect health care costs due to loss of productivity. Direct health-care costs include costs of health-care consumption in general (that is, general practitioner, physical therapists, hospital visits and so on.). The number of consultations is multiplied by the cost of each visit to calculate total costs.

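### The cost-utility ratio is stated without adjustment for baseline EQ-5D and baseline cost, which gives up precision that the collected data could supply

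*Protocol article*

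**What the plan says.** Research question 3 asks for the cost-effectiveness of exposure compared with CBT-P. The Data analysis section answers it with a cost-utility and a cost-effectiveness analysis, and for both "the incremental cost-effectiveness ratio (ICER) was calculated as (C1-C0)/(E1-E0) where C is the cost and E is the effect". The two effects differ. For cost-utility, "The incremental cost-utility ratio will focus on the net costs per quality adjusted life years (QALY) gained". For cost-effectiveness, "The cost-effectiveness ratio focuses on the net costs per reliable and clinically improved case of disability/pain".

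The same section has one covariate provision: "Possible confounding variables (for example, duration of complaints) will be considered and included as covariates according to the results of correlation analyses". It comes directly after the repeated-measures model and before the economic evaluation is introduced. It names neither baseline EQ-5D nor baseline cost.

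The data needed for adjustment are among those planned:

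- Under Secondary outcomes, "Quality of Life is measured using the EuroQol Questionnaire (EQ-5D".
- The Abstract lists costs as a secondary outcome. The Economic evaluation section measures them with a "questionnaire for costs associated with psychiatric illness over the past month (TIC-P".
- Under Data collection, "Data are collected at baseline (T0), after 10 sessions (T1, completion of EXP short), upon completion of the intervention (T2", with a further assessment six months after completion.

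Allocation is stratified by PCS and PDI (Patient allocation and randomization). The article does not say how QALYs are calculated. It gives no SD or correlation for EQ-5D, QALYs or costs.

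**The concern.** The increments in the formula are differences between conditions, and no baseline term is attached to them. If QALYs are accumulated from utilities over time, baseline utility is part of each patient's total and is also correlated with the later values. A chance difference in baseline utility between arms of 36 then passes into the QALY difference. Baseline spending can carry into later costs in the same way. The strata do not directly balance utility or cost.

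The QALY difference is the denominator of the ratio. The treatments are all active, and the sample size section expects only a small effect, so that difference may lie near zero. There a modest shift can change the ratio greatly or reverse its sign. The clinical outcomes are less exposed, because the group-by-time analysis includes baseline as a measurement. The plan states no comparable protection for the cost-utility ratio.

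**Working it through.** **The plan's own figure.** No precision is stated for the ICER. The only design figure is 108 patients (36 per arm), from an effect of 0.2, alpha 0.05, power 0.95 and a correlation of 0.5. The number of measurements m is not given. With m = 2 and 0.2 read as Cohen's f, the noncentrality is 0.2² × 108 × 2 / (1 − 0.5) = 17.28 on 2 and 105 df, and power is 0.965. The minimum in equal groups is 102, and rounding up to full blocks of nine gives 108. So 36 per arm and 0.5 are usable inputs, but the 0.5 was stated for that power calculation, not for EQ-5D.

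**Further inputs.** Sessions are in a "structured, individual setting with weekly appointments of 50 minutes". Visits therefore fall at about weeks 0, 10, 15 and 41 for 15 sessions, and 0, 10 and 36 for 10 sessions. Assumed: QALYs are the trapezoid area under the utility curve, with equal variances and one correlation ρ between visits.

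**QALY difference.** For weeks 0/15/41 the trapezoid weights are 7.5, 20.5 and 13 weeks. In units of the utility variance, at ρ = 0.5:

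- Covariance of baseline utility with the area: 7.5 + 0.5 × (20.5 + 13) = 24.25.
- Variance of the area: 0.5 × (7.5² + 20.5² + 13²) + 0.5 × 41² = 1163.25.
- Share of variance removed by adjustment: R² = 24.25² / 1163.25 = 0.506.
- Standard error ratio: √(1 − 0.506) = 0.703, a fall of 30%. The unadjusted interval is 1/0.703 = 1.42 times as wide.

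| Visits used (weeks) | Variance cut, ρ = 0.3 | ρ = 0.5 | ρ = 0.7 | SE cut, ρ = 0.5 |
|---|---|---|---|---|
| 0, 15, 41 | 32% | 51% | 70% | 30% |
| 0, 10, 15, 41 | 29% | 49% | 69% | 28% |
| 0, 10, 36 | 27% | 46% | 67% | 27% |

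**QALYs as change from baseline.** On weeks 0/15/41 at ρ = 0.5, subtracting 41 weeks of baseline utility makes the covariance 24.25 − 41 = −16.75. The variance becomes 1163.25 − 2 × 41 × 24.25 + 41² = 855.75, so R² = 16.75² / 855.75 = 0.33. The direction of the imbalance effect reverses, but adjustment still helps.

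**Chance imbalance.** With 36 per arm, and ignoring stratification, the standard error of the baseline difference is √(2/36) = 0.236 SD. On weeks 0/10/15/41 at ρ = 0.5, the QALY difference carries 23/52 = 0.44 of it. At an assumed utility SD of 0.25 this contributes 0.44 × 0.25 × 0.236 = 0.026 QALY (one standard error; 95% range ±0.051). The total standard error is 0.037 unadjusted and 0.027 adjusted. For SDs of 0.20 and 0.30 the contribution is 0.021 and 0.031.

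**Cost-utility answer as a whole.** Let s be the share of net-benefit variance due to QALYs and r the correlation of baseline with later cost, with costs and QALYs taken as independent. The variance cut is s × 0.487 + (1 − s) × r². At s = 0.25 and r = 0.2 it is 0.122 + 0.030 = 15% (standard error 8%). At s = 0.75 and r = 0.6 it is 0.365 + 0.090 = 46% (standard error 26%). A cut of about half would need r of about 0.7.

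**The case against.** The strongest reply is that the article gives only the general definition of an ICER. It does not call the increments raw or unadjusted, and regression-adjusted increments fit the same formula. The covariate sentence stands in the same paragraph, and EQ-5D and costs are both secondary outcomes, so it might reach them. A journal article may also leave such detail to a fuller plan.

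Much of this stands as a limit on the point. A reader might infer that the plan fixes a raw ratio; the text does not go that far and does not exclude adjustment. But the article does write down an estimator for research question 3, and it attaches no baseline term. The covariate sentence chooses covariates from the data and does not commit to either baseline measure, so it secures no adjustment in advance.

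Three other stronger readings also fail:

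- **Half the precision is lost.** That is a variance figure, for QALYs only, under a borrowed correlation and an assumed QALY method.
- **The result is biased.** Under randomization a chance imbalance is part of the sampling error, which a valid unadjusted interval already covers. Stratifying on PCS and PDI would reduce it further if these correlate with utility or cost.
- **Both ratios are affected alike.** The improved-case effect already uses each patient's own baseline, so the QALY argument does not reach it.

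**Conclusion.** The point holds as an inexpensive improvement to the cost-utility analysis. Following the formula as written gives a ratio that is open to chance baseline differences and less precise than it need be.

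The gain on the QALY side is material throughout the range examined. It rests on equal correlation between visits, on a correlation that the plan states for another purpose, and on a QALY method that the article does not give. The choice of QALY method changes the size of the gain but not the remedy. For the full cost-utility answer the document supports no single figure; the range of 15% to 46% of variance is illustrative and depends on assumed cost correlations and variance shares.

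**What to change.** In the Data analysis section, for the cost-utility analysis, state that:

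- the QALY increment is the arm coefficient from a regression of QALYs on arm, baseline EQ-5D utility and the PCS and PDI strata;
- the cost increment is the arm coefficient from a regression of total cost on arm, baseline TIC-P cost and the strata;
- uncertainty comes from bootstrapping patients and refitting both regressions in each resample;
- the unadjusted ratio is reported as a sensitivity analysis.

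This costs one or two sentences and two simple regressions. It needs no new patients or visits, given that EQ-5D and the TIC-P are completed at T0 as the article implies. The small downside is that the main ratio is no longer the simple ratio of raw differences in arm means. The article reports 71 of 108 patients randomized by May 2013 and results expected in 2014, so at that stage the wording could still be set before analysis.

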### Objectives

The present investigation, which began recruitment in August 2011 and is currently ongoing, utilizes a three-arm randomized controlled trial method to assess the efficacy of graded *in vivo* exposure (EXP) for CLBP relative to cognitive behavioral therapy (CBT-P). To our knowledge, this is the first study to implement *in vivo* exposure for CLBP patients in an outpatient setting in Germany, and is also the first study to compare graded *in vivo* exposure to CBT. Accordingly, we will assess the feasibility of this new treatment approach. Dose-effects will be analyzed by comparing a short and a long version of EXP. In addition, cost-effectiveness will be evaluated. Besides, the main questions meditational analyses and examination of effects of generalization are planned.

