#### Research questions

1) Is EXP more effective (at post-treatment and at six-month follow-up) at reducing pain-related disability and pain intensity (primary outcomes) as well as other symptoms compared to CBT-P in patients with fear-avoidance beliefs?

2) Are there any differences in treatment effects between the short (10 sessions) and the long (15 sessions) versions of exposure at post-treatment and at six-month follow-up?

3) What is the cost-effectiveness of EXP as compared to CBT-P?

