### Process evaluation

Participants complete a short survey online each week to measure mediating variables relevant to the process of change. The battery includes the TSK, PDI, IPAQ, QBPDS, a numeric rating scale assessing pain severity, and an 11-item scale assessing coping with pain, self-efficacy and avoidance rated on an 11-point scale.

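### The plan assigns the dose-response question to a probit on response rates and does not say that the long v short conclusion rests on the continuous scores, where power would be higher

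*Protocol article*

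**What the plan says.** Three parts of the protocol article bear on this.

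- **The question.** Objectives says: "Dose-effects will be analyzed by comparing a short and a long version of EXP". Research question 2 asks: "Are there any differences in treatment effects between the short (10 sessions) and the long (15 sessions) versions of exposure", at post-treatment and at six months.
- **The method named for dose-response.** Data analysis says: "Probit analysis will be used for dose–response effects". It adds that the approach "includes determining the observed rates and resulting probability of a response for a particular treatment". The outcome of this analysis is therefore a response or no response per patient.
- **The general model.** The same section says: "A repeated measures design will be used with primary and secondary measures as dependent variables, group as the between-subjects factor". Time is the within-subjects factor, and Cohen's d is planned for mean differences between groups. The two exposure versions are two of the three groups.

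Two responder ideas appear nearby, and neither is tied to the probit. On pain: "We consider a 30% reduction on the NRS to indicate clinically important change". For the cost-effectiveness ratio, the unit is "net costs per reliable and clinically improved case of disability/pain".

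**The concern.** The primary measures (PDI, QBPDS, 0-10 pain ratings) are scores. A probit on response rates keeps only which side of a cut each patient falls on and discards the size of the change. For the same contrast between the same two arms, that costs power.

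The long v short comparison has about 36 patients per arm, and the Discussion treats its result as decisive for an effective and economical treatment length. If the analysis labelled dose-response carries the conclusion, a real benefit of the five extra exposure sessions is more likely to be missed. If the probit and the continuous contrast disagree, the text gives no order of precedence, and its wording points to the less precise of the two.

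**Working it through.** **The plan's own figure.** The sample size section gives 36 per group (108 in total) for a three-group group x time effect of 0.2, alpha 0.05, power 0.95 (printed as β) and correlation 0.5. Reading 0.2 as Cohen's f with m = 2 measurements, the noncentrality is N·m·f²/(1−ρ) = 108 × 2 × 0.04 / 0.5 = 17.28 on 2 and 105 df, which gives power 0.965. The smallest N in equal groups for 0.95 is 102, and 108 is the next multiple of the block size of nine. The number of measurements behind 108 is not stated, so this is a plausibility check and not an exact reproduction. Nothing below depends on it. No effect size, response rate or power is stated for long v short or for the probit.

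**Inputs.**
- From the protocol: 36 per arm, two-sided 0.05. Last value carried forward keeps all patients in the analysis.
- Assumed: a true long v short difference d of 0.2 to 0.8 SD (the span of the Cohen scale cited in Data analysis); a short-arm response rate of 30-50%; normal scores with equal SD; response defined by a cut on the same score; the probit run across the two randomised arms.

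**Formulae.**
- Full scale: two-sample t-test, 70 df, noncentrality d·√(36/2), critical value 1.994.
- Response: with short-arm rate p₁, the long-arm rate is p₂ = Φ(Φ⁻¹(p₁) + d). With only two doses, testing the probit slope amounts to comparing two proportions. Power is the exact binomial probability that the pooled two-proportion z statistic exceeds 1.96.

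**Example, d = 0.5, p₁ = 0.40.** The noncentrality is 0.5 × √18 = 2.12, so full-scale power is 55.3%. For the response, p₂ = Φ(−0.253 + 0.5) = 0.597 and power is 37.4%. The loss is 55.3 − 37.4 = 17.9 points (17.8 before rounding).

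| d | Full-scale power | Response power, p₁ 30-50% | Loss (points) |
|---|---|---|---|
| 0.2 | 13% | 10-11% | 3-4 |
| 0.3 | 24% | 16-17% | 7-8 |
| 0.5 | 55% | 37-38% | 17-18 |
| 0.7 | 83% | 64% | 20 |
| 0.8 | 92% | 75% | 17 |

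**Cross-checks.** Simulating 100,000 trials per cell with the probit test itself, at p₁ of 30% and 50%, gives losses of 6.8-8.1 points (likelihood ratio) and 8.1-8.6 (Wald) at d = 0.3, and 17.1-17.3 and 18.6-19.0 at d = 0.5. The large-sample efficiency of a cut, φ(z)²/[p(1−p)], is 0.58 at 30% and 0.64 at 50%, so 36 patients carry the information of about 21 to 23. With response rates widened to 20-60% and normal approximations for both tests, the loss is 3.5-4.5 points at d = 0.2 and 18-22 at d = 0.5.

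**The case against.** The strongest reply is that the continuous comparison is already planned. Both exposure arms are in the repeated measures model, Cohen's d is planned for group differences, and research question 2 reads naturally as a contrast in that model. The sentence on the probit does not say that it replaces this contrast. That stands. A reader might infer that the trial as a whole gives up the tabulated power for long v short, or has no full-scale comparison of the two versions. The documents do not support either inference: the loss applies only to the probit.

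A second reply is that the probit answers a different question. The Problem definition section asks how many sessions are needed and cites a benchmark expressed as the share of patients who improve. A probability of response is a legitimate quantity, and a yes/no outcome is built into it. That also stands, and it is a reason to keep the probit. It does not make the probit the better basis for research question 2, which asks about differences in treatment effects.

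A third reply is that the power figures rest on assumed inputs and on a two-arm reading of the probit. That is correct. At 0.2 SD the loss is small, and power is only 13% even on the full scale. The missing definition of response for the probit is a detail that an article may leave to the full plan, and it is not held against the trial here.

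What remains is the allocation. Dose effects are defined as short v long, dose-response is given by name to the probit, no long v short contrast is named in the general model, and neither analysis is given precedence.

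**Conclusion.** The point holds in a limited form. The method named for dose-response works on a coarser scale than the outcomes it concerns, and the plan does not say that the dose conclusion rests on the continuous contrast. If the probit carries the conclusion, the loss grows from a few points of power at a small true difference to about 20 at 0.7 SD, on the assumptions listed above. The size for this trial cannot be fixed more closely, because the protocol states neither a long v short effect nor a response rate. If the continuous contrast carries the conclusion, this power is not lost. The point is worth a change because the change is cheap and the dose question is one of the trial's three research questions. It is not an error that invalidates the analysis.

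**What to change.** In Data analysis, state that the dose-response conclusion rests on the EXP_long minus EXP_short difference, with its 95% confidence interval, in the continuous PDI, QBPDS and pain scores at post-treatment and at six months, taken from the planned repeated measures model. Keep the probit as a supportive description of the probability of response.

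The cost is a sentence or two and one named contrast. The scores are already collected at the planned assessments, so no new data are needed. The one downside is that the probability-of-response figure becomes supportive and no longer leads the dose result.
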